**5.2 Exclusion Criteria**

- 5.2.1 Profound neutropaenia considered to preclude administration of ganciclovir or profound renal failure considered to preclude administration of foscarnet
- 5.2.2 Inability to give informed consent
- 5.2.3 In the stem cell group, Donor negative, Recipient negative transplants.
- 5.2.4 In the stem cell group: matched unrelated donors who are CMV seronegative
- 5.2.5 Those patients who have been in Group A cannot then enter the Group B part of the study.
- 5.2.6 Those patients who have been in Group B cannot then enter the Group A part of the study.

**6. Study Procedure and Assessments****6.1 CMV Monitoring**

All patients will be monitored by citrated or EDTA peripheral blood samples for CMV PCR viral load twice weekly as part of routine clinical care. Personnel performing the CMV PCR viral load monitoring will be blinded to which arm of the study the patient is on.

**6.2 Biochemistry and Haematological Monitoring**

All patients recruited to the trial will have routine full blood counts, biochemistry and renal function as part of clinical care and the results will be used by the clinicians to adjust the doses of preemptive therapy.

**6.3 Immune Function**

24 ml Blood will be taken on two occasions before becoming PCR negative to monitor for CMV-specific immune function, including ELISPOT, intracellular cytokine assay and CMV specific MHC Class I tetramers.

#### 6.4 Treatment

Patients will be prescribed preemptive therapy at the discretion of the responsible clinician, using drugs and dosages appropriate for each patient. For example, full doses include ONE of the following: valganciclovir 900mg bd; OR ganciclovir 5mg/Kg iv bd; OR foscarnet 90mg/Kg iv bd; OR foscarnet 60mg/Kg tds; OR ganciclovir 5mg/Kg iv od PLUS foscarnet 90mg/Kg iv od. In all cases, doses will be reduced according to estimated creatinine clearance (foscarnet, valganciclovir and ganciclovir) or neutropenia (valganciclovir and ganciclovir).

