## **2. Background and Study Rationale**

In transplant recipients with CMV infection, the risk of developing CMV disease is directly proportional to the CMV DNA viral load. Historically at this Institution, patients were given preemptive therapy on the basis of two consecutive positive CMV PCR results as detected by a qualitative PCR technique. With the introduction of real time PCR, using a Taqman probe and the ABI7700 thermal cycler, it is possible to obtain rapid and sensitive results of viral load on clinical samples with a lower limit of detection of 200 copies/ml. Thus, viral load data can be incorporated into the clinical management of the patient.

From our natural history data, it has been shown that patients with CMV disease had a CMV PCR load ranging from 14,000 to 203 million (median 175,500). The lower bound of the 95% confidence limits of this distribution was 37,000 copies/ml and we aimed to initiate therapy in time to prevent CMV viral load reaching this value. To give a margin of safety, bearing in mind the 1 day average doubling-time of CMV and the timing of sampling twice-weekly, we therefore recommended that preemptive therapy be given once the viral load increases above 3,000 copies/ml. In the past, all patients with a CMV PCR load between 200 and 3,000 copies/ml have received preemptive treatment because the previous PCR assay did not give a quantitative result. As treatment is associated with side effects such as neutropaenia (ganciclovir) and renal impairment (foscarnet) it would be preferable to avoid unnecessary exposure where possible. This study aims to determine: a) whether those patients with 'low level' viral load results (between 200 and 3,000 copies/ml) could be monitored as opposed to starting preemptive therapy with valganciclovir, ganciclovir and/or foscarnet; b) whether those patients with 'high level' viral load results (above 3,000 copies/ml) could stop preemptive therapy earlier, thus maximising the benefits of therapy and minimising its risks.

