## **3. Objectives**

### **3.1 Primary Objectives**

- 3.1.1 To define the number of patients in Group A with a low level of CMV reactivation who subsequently develop a viral load greater than 3000 copies/ml
- 3.1.2 To define the number of patients in Group B who develop a second episode of a viral load above 3000 copies/ml after therapy has been discontinued at the defined viral load cut-offs.

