**Group A:**

Patients with two consecutive CMV viral loads between 200 and 3000 copies/ml in the renal, liver and stem cell groups will be randomised to receive immediate pre-emptive therapy or continue with frequent CMV PCR monitoring twice weekly, commencing pre-emptive therapy only if viral load exceeds 3000 copies/ml.

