## **9. Statistical Considerations**

The primary end point is the number of patients in whom viral load increases above 3,000 copies/ml (requires a second discrete episode from patients in group B).

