### **9.1 Sample size considerations.**

For Group A, our historical data show that no patients developed CMV disease when they were treated with low viral loads. If we assume that only 1% will develop viral loads >3000 copies/ml after starting treatment and that a rate of 25% or more requiring treatment among those allocated to monitoring would be a failure, then a study size of 72 (36 + 36) patients has 90% power to detect this difference ( $\alpha < 0.05$ ).

For Group B, our historical data show that 30% of patients require a second course of preemptive therapy. This trial would be a failure if this proportion doubled to 60% or more. A study size of 106 (53 + 53) patients has 90% power to detect this difference ( $\alpha < 0.05$ ).

The data will therefore be analysed when 72 patients have been recruited and followed in Group A and 106 recruited and followed in Group B. No interim analyses are planned.

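### Group B counts only a second load above 3,000 copies/ml but is sized on second courses of therapy, and with no restart load fixed, a patient re-treated below 3,000 scores as a success

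*Protocol*

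**What the plan says.** **Endpoint.** Section 9 defines it as "the number of patients in whom viral load increases above 3,000 copies/ml (requires a second discrete episode from patients in group B"). The Group B objective in Section 3.1 matches: "To define the number of patients in Group B who develop a second episode of a viral load above 3000 copies/ml after therapy has been" stopped at the defined cut-offs. Re-treatment is not part of either definition.

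**Sizing.** Section 9.1 takes its Group B control rate from a treatment event: "our historical data show that 30% of patients require a second course of preemptive therapy". Failure is a doubling to 60% or more. The stated size is 53 + 53 for 90% power.

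**Start, stop and restart.** Section 4 stops therapy in one Group B arm after two consecutive loads under 3,000, and in the other after two consecutive negative results (under 200). It gives no load for restarting in either arm. For the monitored arm of Group A, by contrast, it does fix one: "commencing pre-emptive therapy only if viral load exceeds 3000 copies/ml". Section 6.4 adds: "Patients will be prescribed preemptive therapy at the discretion of the responsible clinician", and the sentence goes on to the choice of drug and dose for the individual patient.

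**Past practice.** Section 2 reports that patients formerly received "preemptive therapy on the basis of two consecutive positive CMV PCR results as detected by a qualitative PCR technique", and that loads of 200 to 3,000 were therefore all treated.

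**Blinding.** Treatment is open label (Section 4). Only the staff who run the PCR are blinded to arm (Section 6.1).

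**The concern.** Two gaps combine.

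First, the event used for sizing and the event used for analysis are worded differently, and nothing links them. Because loads of 200 to 3,000 were once treated, the historical 30% may include second courses given to patients who never exceeded 3,000. If so, 30% is too high for the endpoint as defined.

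Second, Group B has no stated restart load. Someone re-treated at, for example, 2,000 copies/ml has had a second course, yet is counted as a success unless the load later passes 3,000. The early-stop arm leaves therapy while virus may still be detectable; the other arm leaves it only when PCR is negative. Clinicians know the arm and see results twice weekly. Restarts below the threshold are therefore plausibly more frequent in the early-stop arm, and each one that prevents a crossing removes an event from the arm under test. The trial asks whether early stopping causes too many failures, so the error runs towards false reassurance.

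**Working it through.** **1. The plan's own figure.** Inputs from Section 9.1: 30% v 60%, alpha 0.05, 90% power. The protocol does not state the number of sides; two-sided reproduces its figure. With unpooled variance:

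n per arm = (1.960 + 1.282)² × (0.30 × 0.70 + 0.60 × 0.40) / (0.60 − 0.30)² = 52.5, so 53 per arm and 106 in all.

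This matches the plan. The sample-size arithmetic is not at fault.

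**2. Baseline power.** Exact enumeration of the two binomials with 53 per arm, two-sided 0.05, gives 88% for the chi-square test (84% for Fisher's exact test). Expected events are 53 × 0.60 = 31.8 in the early-stop arm and 53 × 0.30 = 15.9 in the other.

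**3. Effect of pre-empted events.** Let x be the share of would-be second loads above 3,000 that are prevented by re-treatment below 3,000. The documents give no value, so the range is an assumption. The true rates are held at 60% and 30%.

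- Early-stop arm only: observed rates are 0.60 × (1 − x) v 0.30.
- Both arms equally: observed rates are 0.60 × (1 − x) v 0.30 × (1 − x).

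| x (assumed) | Early-stop events removed (31.8x) | Rates, early-stop arm only | Power | Rates, both arms | Power |
|---|---|---|---|---|---|
| 0 | 0 | 60% v 30% | 88% | 60% v 30% | 88% |
| 10% | 3.2 | 54% v 30% | 71% | 54% v 27% | 82% |
| 20% | 6.4 | 48% v 30% | 49% | 48% v 24% | 75% |
| 33% | 10.6 | 40% v 30% | 20% | 40% v 20% | 63% |
| 50% | 15.9 | 30% v 30% | 5% | 30% v 15% | 47% |

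Power is by exact enumeration with the chi-square test. In the one-arm case at 50% the observed rates are equal, so the 5% is simply the size of the test.

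**4. Reading the two cases.** Equal pre-emption leaves the ratio at 2 and costs power only. Unequal pre-emption also shrinks the observed difference, and that is the bias. The truth may lie between them: a patient who stopped on negative results and reappears at 200 to 3,000 also has no restart load to govern treatment.

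**The case against.** **Section 6.4 concerns regimen choice.** The sentence continues to drugs and dosages, and the rest of the section lists regimens and dose reductions. A reader might infer that it lets clinicians restart at any load, or that it contradicts Section 4. The text does not support either; its most natural meaning is choice of drug and dose. This stands. What remains is that no section sets a restart load for Group B.

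**The protocol treats needing therapy as exceeding 3,000.** Sections 2 and 5.1.3 link therapy to that threshold, and the Group A paragraph of Section 9.1 uses the two ideas for one comparison. The Group B 30% may therefore mean second loads above 3,000. A reader might infer instead that it was counted under the old rule of treating any two positive results. Section 9.1 gives no period, assay or trigger, so neither reading is established.

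**The loss may be small.** With the one-day doubling time in Section 2, a rise from 200 to 3,000 takes log2(3,000/200) = 3.9 days, about one interval of twice-weekly sampling. A fast rebound leaves little time to intervene; slow or persistent low-level viraemia leaves more. Nor does every restart prevent a crossing. This stands, and the upper end of the range should not be read as a forecast. In particular, the statement that the doubling disappears needs 50% pre-emption confined to one arm, for which the documents give no support.

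**Counting restarts brings its own bias.** The load is measured by blinded staff; a restart is an unblinded decision and may count against early stopping. This stands, and is why restarts should not enter the primary endpoint.

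**Group A.** A reader might extend the point to treatment started below 3,000 in the monitored arm. That does not carry over: Section 4 fixes the start load there, and the comparator is treated below 3,000 by design, so such an event could not be defined alike in both arms.

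**Conclusion.** The point holds for Group B. The sizing event and the endpoint are worded differently, no restart load is stated, and re-treatment below 3,000 without a later crossing scores as a success. If such re-treatment is commoner in the early-stop arm, the bias favours early stopping.

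The size is conditional. On an assumed 10% to 50% of events pre-empted, power falls from 88% to between 71% and 5% if only the early-stop arm is affected, and to between 82% and 47% if both arms are affected equally. These figures assume true rates of 60% v 30%, 53 per arm, a two-sided chi-square test, and x defined as events actually prevented. Neither the frequency of early restarts nor the trigger behind the 30% can be read from the protocol. The finding is a gap that can mislead, not a demonstrated failure of the trial.

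**What to change.** - Keep the load above 3,000, measured by blinded laboratory staff, as the primary endpoint.
- In both Group B arms, record every restart of an anti-CMV drug after discontinuation, with its date and the viral load at that time.
- Pre-specify a key supportive analysis of the first of (a) a load above 3,000 or (b) any restart, with each component shown by arm. Do not conclude that early stopping is acceptable unless this and the primary analysis agree.
- State in Section 9.1 whether the 30% refers to second courses of therapy or to second loads above 3,000.
- Reconcile the Group B rules in Section 4, the treatment text in Section 6.4, the endpoint in Section 9 and the sizing in Section 9.1 on re-treatment in Group B. Which clinical rule applies is for the investigators.

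The cost is a few lines of protocol text, two recorded items per restart and one added analysis. The downside is small: the restart component is an open-label decision that may count against early stopping, hence its supportive role and separate display.

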### 7. Assessment of Safety

Adverse events and serious adverse events occur frequently in these seriously ill patients, unrelated to the use of ganciclovir or foscarnet and these will not be recorded or reported. Transplant patients are discussed at weekly, multi-disciplinarily ward rounds and their medical history will be reviewed for any occurrences of serious adverse events or SUSARs (see definitions below) which are deemed attributable to the use of preemptive therapy. Any such SAEs or SUSARs will be reported to the sponsor, the ethics committee and the MHRA using a standard form.

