#### Definition of an Adverse Event

An AE is any untoward medical occurrence in a subject to whom a medicinal product has been administered including occurrences which are not necessarily caused by or related to that product.

An AE can therefore be any unfavourable and unintended sign, symptom or disease temporally associated with the use of a medicinal product, whether or not considered related to the medicinal product.

The worsening of an existing sign or symptom is also considered an AE.

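### Section 7 records only serious events attributed to antiviral therapy, so CMV disease, death and graft loss after deferred or earlier-stopped therapy fall, by inference, outside what the trial collects

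*Protocol*

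**What the plan says.** Section 7 of the protocol calls adverse and serious adverse events frequent in this population, "unrelated to the use of ganciclovir or foscarnet and these will not be recorded or reported". Patients' histories are to be "reviewed for any occurrences of serious adverse events or SUSARs (see definitions below) which are deemed attributable to the use of preemptive therapy". The reporting sentence covers the same subset: "Any such SAEs or SUSARs will be reported to the sponsor, the ethics committee and the MHRA using a standard form".

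The definition of an adverse event further on in section 7 is wider, "including occurrences which are not necessarily caused by or related to that product", but it applies only to a subject who has been given a medicinal product. The list of seriousness criteria includes death.

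Section 2 gives the reason for the trial: "As treatment is associated with side effects such as neutropaenia (ganciclovir) and renal impairment (foscarnet) it would be preferable to avoid unnecessary exposure". It also derives the 3,000 copies/ml treatment threshold from the viral loads of patients who had CMV disease.

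Section 6.2 states that "All patients recruited to the trial will have routine full blood counts, biochemistry and renal function as part of clinical care", with the results going to clinicians for dose adjustment.

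The objectives (sections 3.1 and 3.2) and the primary endpoint (section 9) cover viral load above 3,000 copies/ml, duration of therapy, rate of viral load increase and immune function. CMV disease, death, graft loss, neutropaenia and renal impairment do not appear there.

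**The concern.** In both groups the arms differ in how much antiviral the patient receives. Giving more risks drug toxicity. Giving less risks CMV disease and what follows from it. Section 7 is built around the first risk only. An event brought about by the absence of drug cannot sensibly be attributed to the drug, so the attribution filter removes the clinical harm that the less-treated arm might suffer.

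If the rule is followed, the trial could end with a recommendation to defer or shorten therapy without having counted CMV disease, the outcome that therapy is meant to prevent. A reader shown attributed serious events by arm would see a count to which the more-treated arm can contribute more easily. The milder toxicity that motivates the trial would also be absent from its planned data.

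**Working it through.** No figure in the protocol is in dispute, so the check is mainly a reading of the sections side by side.

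**1. What is captured, and where**

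| Event | Objective or endpoint (sections 3, 9) | Section 7 | Other source |
|---|---|---|---|
| Viral load above 3,000 copies/ml (second episode in Group B) | Yes, primary | n/a | Twice-weekly PCR, 6.1 |
| Duration of antiviral therapy | Yes, 3.2.1 | n/a | n/a |
| Serious event attributed to therapy | No | Yes | n/a |
| CMV disease, death or graft loss after deferral or earlier stopping | No | No, by inference: not attributable to the drug | None named |
| Non-serious neutropaenia or renal impairment | No | No: not serious | Routine bloods, 6.2, not planned as trial data |

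**2. How the filter acts on each arm.** In Group A, a monitored patient who never exceeds 3,000 copies/ml does not start preemptive therapy under the protocol. No event in that patient can be deemed attributable to it, so the patient cannot add to the section 7 count. A patient treated at once can. In Group B both arms receive drug, but the earlier-stopping arm is meant to receive it for less time, so the imbalance is in the same direction. Section 4 makes the trial open label; section 6.1 blinds only those running the PCR. Attribution would therefore be made knowing the arm.

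**3. CMV disease in the protocol's own reasoning.** Section 2 ties the risk of CMV disease to viral load and sets the threshold to keep loads below 37,000 copies/ml. Section 9.1 opens the Group A justification with historical experience of no CMV disease in patients treated at low loads. The trial plans no data that could be set against that benchmark.

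**4. Plausibility on the protocol's figures.** Inputs from section 2: average doubling time 1 day, sampling twice weekly, lowest load seen with disease 14,000 copies/ml. Assumption: samples 3 or 4 days apart. Load at the next sample = starting load × 2^days. From just under 3,000:

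- 3 days: 3,000 × 2³ = 24,000
- 4 days: 3,000 × 2⁴ = 48,000

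Both exceed 14,000, and the second exceeds 37,000. This is no argument about the threshold. It shows only that, on the protocol's figures, disease in a monitored patient is not so remote that it can go unrecorded.

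**5. What full recording could show.** With zero events among n patients, the exact two-sided 95% upper limit is 1 − 0.025^(1/n):

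- n = 36: 9.7%
- n = 53: 6.7%

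These limits do not measure the defect. They show that even complete recording with no events would give only moderate reassurance. A zero obtained under a rule that excludes such events gives none.

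**The case against.** The strongest reply is that the trial already measures the direct consequence of giving less therapy. Viral load above 3,000 copies/ml is the primary endpoint, PCR is twice weekly, monitored Group A patients start therapy on crossing the threshold, and section 2 presents that threshold as an early warning set well below the loads seen in disease. Section 7 does not mention CMV disease, and the class it sets aside reads as background illness in very sick patients. The protocol also gives a practical reason for not recording everything: such events are frequent.

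Much of this stands, and it rules out several stronger readings that a reader might infer:

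- *That every harm of withholding or stopping goes unrecorded.* The virological harm is recorded; the gap is in clinical harm.
- *That the protocol contains a biased safety comparison.* It states no between-arm safety analysis. The danger lies in how attributed events might later be read.
- *That the trial cannot show the benefit it seeks.* Its primary objectives are virological, duration of therapy is objective 3.2.1, and less exposure is the stated route to fewer side effects.
- *That toxicity data are lost, or that bloods serve dosing alone.* Section 6.2 does not say so, and the results remain in routine records for all recruited patients.
- *That every serious event must be recorded whatever its cause.* The stated frequency of such events is a fair reason not to require this.

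What the reply does not meet is that a viral load crossing is not disease, death or graft loss, and that section 7, applied as written, gives no route for those events into the trial record. A statistical analysis plan could set laboratory cut-offs and tables, but it cannot analyse clinical events that the protocol says will not be recorded.

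**Conclusion.** The point holds for clinical harm. Section 7 fixes a recording rule under which CMV disease, death and graft loss following less therapy are not captured unless attributed to the drug, and no objective or endpoint recovers them. It bears on the 36 patients allocated to monitoring in Group A and the 53 allocated to earlier stopping in Group B, and on any comparison with their controls. How many events would be missed cannot be estimated, because the protocol gives no rate of CMV disease, death or graft loss for these strategies.

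The conclusion rests on two assumptions: that the rule is applied as written, and that clinicians would not attribute an event arising from too little drug to the drug itself. The second is an inference, since section 7 does not name these events. The primary comparison and the sample sizes are untouched. What is lost is the ability to set clinical harm against the treatment avoided, which is the benefit-risk question that section 2 raises. The missing toxicity data are the lesser part, because they can be retrieved.

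**What to change.** Amend section 7 so that CMV disease, death and graft loss are recorded for every randomised patient in both arms of Groups A and B, regardless of attribution and of whether any antiviral was given, over the same follow-up period, and tabulated by randomised arm. The protocol gives no length of follow-up (section 9.1 speaks only of patients being recruited and followed), so the amendment must state the period.

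Extract neutrophil counts and renal function from the routine bloods under section 6.2, and compare neutropaenia and renal impairment by arm using laboratory cut-offs fixed in advance. Present these beside the duration of therapy already collected under 3.2.1.

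Attribution may continue to govern expedited reporting and the recording of other serious events, which keeps the burden that section 7 is concerned about in check.

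The cost is a protocol amendment, a short case report form and a modest workload in extracting data from routine records. No treatment rule, visit or sample size changes.
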